## EXECUTIVE SUMMARY

|                             |                                                                                                                                                                                                                                                                                                                                                                                                                                                                                              |
|-----------------------------|----------------------------------------------------------------------------------------------------------------------------------------------------------------------------------------------------------------------------------------------------------------------------------------------------------------------------------------------------------------------------------------------------------------------------------------------------------------------------------------------|
| TITLE                       | Comparison of a new GE LEHRS vs Siemens LEHR collimator on image quality in scintigraphy.                                                                                                                                                                                                                                                                                                                                                                                                    |
| ACRONYM                     | LEHRS                                                                                                                                                                                                                                                                                                                                                                                                                                                                                        |
| PROPONENT                   | CHR ORLEANS
[name]
[name]                                                                                                                                                                                                                                                                                                                                                                                                                       |
| PRINCIPAL INVESTIGATOR      | [name] [name]
CHR ORLEANS
Nuclear medicine department
[name]
[name]                                                                                                                                                                                                                                                                                                                                                            |
| PROTOCOL VERSION            | V1.0 of February 1, 2018                                                                                                                                                                                                                                                                                                                                                                                                                                                                     |
| RATIONALE / CONTEXT         | Performances of a monophotonic scintigraphic examination with a gamma camera requires the use of a collimator. This perforated grid is the subject of industrial studies to find the best compromise between, on the one hand, the size and number of "holes" (determining sensitivity) and, on the other hand, the thickness and length of septa (conditioning the resolution). These parameters are inversely linked because the increase of septa thickness reduces the aperture surface. |
| MAIN OBJECTIVE              | Compare image quality obtained with the new LEHRS GE collimator versus a standard Siemens LEHR collimator in bone scan studies.                                                                                                                                                                                                                                                                                                                                                              |
| SECONDARY OBJECTIVES        | Evaluation of image quality in pulmonary, thyroid, parathyroid and brain scans with DaTSCAN.

Performances evaluation on physical measurement phantoms.                                                                                                                                                                                                                                                                                                                                |
| MAIN JUDGMENT CRITERION     | Rate of images obtaining a score greater than or equal to 4 on visual image quality analysis (on a 5-point LIKERT scale).                                                                                                                                                                                                                                                                                                                                                                    |
| SECONDARY JUDGMENT CRITERIA | Signal-to-noise ratio measurements on patient acquisitions.

Physical performances of the new LEHRS collimator using physical measurement phantoms.                                                                                                                                                                                                                                                                                                                                    |
| METHODOLOGY / STUDY DESIGN  | Monocentric, comparative, non-inferiority study with intra-patient comparisons                                                                                                                                                                                                                                                                                                                                                                                                               |
| CRITERIA FOR INCLUSION OF   | Patients referred to the department for bone, lung, thyroid,                                                                                                                                                                                                                                                                                                                                                                                                                                 |

|                                        |                                                                                                                                                                                                                                                                                                                                                                                   |
|----------------------------------------|-----------------------------------------------------------------------------------------------------------------------------------------------------------------------------------------------------------------------------------------------------------------------------------------------------------------------------------------------------------------------------------|
| SUBJECTS                               | parathyroid or brain scans with DaTSCAN.                                                                                                                                                                                                                                                                                                                                          |
| CRITERIA FOR NON-INCLUSION OF SUBJECTS | Children, pregnant women or women at risk of pregnancy, Patients under guardianship or under trusteeship, known renal failure, patients with pain, patients who cannot have a standard good quality scintigraphic examination.                                                                                                                                                    |
| STRATEGIES / PROCEDURES                | The patient's scans will be performed on 2 separate devices and the images obtained will be compared.                                                                                                                                                                                                                                                                             |
| NUMBER OF PATIENTS                     | 85 patients including 70 for bone scans                                                                                                                                                                                                                                                                                                                                           |
| DURATION OF THE SEARCH                 | Duration of the inclusion period: 1 year

Duration of participation for each patient: less than half a day.

Total duration of the study: 12 months (data inclusion and analysis)                                                                                                                                                                                     |
| EXPECTED BENEFITS                      | As individual for the patient: likely to improve the image quality of his examination, interpretation of the examination by 2 expert doctors.

Collectively: improvement of image quality of scintigraphic exams with this collimator allowing to reduce the duration of exam and/or the injected activity of radiopharmaceutical drugs (improvement of patient dosimetry). |

[figure not shown]

## LIST OF ABBREVIATIONS

---

Table to be completed according to the content of the following protocol

|         |                                                                 |
|---------|-----------------------------------------------------------------|
| ANSM    | National Agency for the Safety of Medicines and Health Products |
| MA      | Marketing Authorization                                         |
| ARC     | Clinical Research Associate                                     |
| BPC     | Good Clinical Practices                                         |
| CPP     | Committee for the Protection of Persons                         |
| CNIL    | Commission Nationale de l'Informatique et des Libertés          |
| CRF     | Case Report Form (observation book)                             |
| EvIG    | Serious Adverse Event                                           |
| ISG     | Serious Adverse Effect                                          |
| EIGI    | Unexpected Serious Adverse Effect                               |
| GE      | General Electric Healthcare                                     |
| ICH     | International Conference on Harmonization                       |
| FDI     | Nurse State graduate                                            |
| INSERM  | National Institute of Health and Medical Research               |
| LEHR    | Low Energy High Resolution                                      |
| MR      | Reference Methodology                                           |
| CPR     | Summary of Product Features                                     |
| SUSAR   | Suspected Unexpected Serious Adverse Reaction                   |
| TEC     | Clinical Study Technician                                       |
| CT SCAN | Computed tomography                                             |

# 1. GENERAL INFORMATION

---

## 2. CONTEXT AND SCIENTIFIC JUSTIFICATIONS

---

Scintigraphic examinations allow to map, in vivo, the biodistribution of a radiopharmaceutical drug, an analogue of a molecule of interest.

Image of the distribution, in the body, of the radiopharmaceutical drug is obtained by detecting the gamma rays emitted by the radioelement used for its marking.

The addition of a collimator (perforated grid) in front of the detectors is needed to select the most informative gamma photons whose direction is orthogonal to the detector.

The choice of the collimator used is based on a compromise between two parameters:

- The thickness and depth of septa. Higher is the energy of the emitted gamma photon (specific to each radioelement), higher is the probability that this photon will pass through material, especially the walls (septa) of the collimator. This septal penetration reduces the spatial resolution and image quality. For this reason, collimators are classified into three main categories, according to the increasing thickness of their septa : low energy (LE), mean energy (ME) and high energy ("high energy" HE)
- The width and number of holes. Large holes increase the sensitivity of the gamma camera but reduce the number or thickness of septa for a constant detector surface. A good sensitivity allows to reduce the examination time but with an alteration of the resolution.

The majority of nuclear medicine examinations use radiopharmaceutical drugs (labelled with technetium 99m, emitting gamma photons, 140keV energy peak) and require the use of low energy collimators (LE). There are large versions of this kind of collimators, the first one promotes sensitivity and the second one promotes resolution (LEHR for "Low Energy High Resolution").

We want to evaluate a new intermediate kind of collimators (LEHRS for "Low Energy High Resolution and Sensitivity", GE) which is design to enhance sensitivity without compromising resolution. The expected degradation of the resolution is compensated by computer correction algorithms.

## **2.1. PATHOLOGY DESCRIPTION**

Bone scan is a common practice examination in nuclear medicine. The radiopharmaceutical drug used in this study is a technetium-99m labelled biphosphonate (in our department, it is hydroxydiphosphonate or HDP-99mTc).

It is an examination that significantly quantifies bone anabolism in response to pathologies and allows a whole body scan in a single examination.

Bone diseases are multiple and can be of tumor, traumatic, rheumatic or infectious origin. Indications for bone scans are varied: rheumatological and orthopaedic (exploration of diffuse bone pain, assessment of inflammatory rheumatism, dating of fractures, research of algoneurodystrophy, exploration of pain on prostheses, in particular research on loosening...), oncological (assessment of extension of bone tumours, in particular tumours with osteocondensing metastases as in prostate cancers, assessment of extension of sarcoma and other bone tumours...)

The main advantages of bone scanning are based on good accessibility of the technique (unlike MRI), its exploration of the whole body, in a reduced examination time (whole body scanning in about 15 minutes), for a relatively low irradiation compared to the diagnostic contribution of the technique. For an adult of 70 kg, the effective dose is 4mSv; for comparison, the natural irradiation in Orléans (related to cosmic and terrestrial radiation from the soil) is about 1 to 2 mSv per year. A thoraco-abdomino-pelvic scanner delivers an average effective dose of 18 mSv according to the 2010 IRSN report "Doses delivered to patients in CT and conventional radiology".

It is also important to note that, unlike radiology examinations, irradiation of scintigraphy is related to radiopharmaceutical drug posology and therefore does not increase with the number of scintigraphic acquisitions performed.

## **2.2. DESCRIPTION OF THE STRATEGY STUDIED**

Exam protocol will be conforme to French and international medical societies recommandations. According to indication, early images will be realized after radiopharmaceutical drug injection. Late bone scan images will systematically be realized 2 hours after injection (for the radiopharmaceutical drug used in our department), mentioned as whole-body scan. This acquisition is often complemented by additional planar acquisitions, focused on a region of interest (most often the painful area and/or pathologic bone uptake).

In some cases, a tomoscintigraphy will be performed, allowing to obtain 3D volume scintigraphy images, improving the sensitivity of detection of small abnormal bone fixations. This acquisition of tomoscintigraphy will be associated with CT scans for more accurate anatomical localization.

In addition to this standard examination, the patient's participation in the research protocol will involve the creation of complementary images with the new collimator : a second whole body

[figure not shown]

scan, a static acquisition, and in cases where it has been requested for the standard examination, a tomoscintigraphy (without CT in this case, to maintain dosimetry equivalent to the standard examination).

## **2.3. SUMMARY OF RESULTS OF AVAILABLE NON-CLINICAL AND CLINICAL TRIALS**

No study has yet been realized to evaluate this new collimator.

Few data from the literature are available on the evaluation of new collimators in nuclear medicine. Most studies are medical physics studies with evaluation of performances in terms of sensitivity and resolution on physical measurement objects (e.g., evaluation of a new collimator in mammary tomosynthesis, Gilland et al. Med Phys 2017 Nov;44(11):5740-5748). An evaluation of the old and new collimator on physical measurement objects is planned in our study.

Our research work can be compared to the studies realized after the commercialization of solid-state nuclear medicine cameras (known as CZT, for cadmium-zinc-telluride). For example, in the retrospective study conducted by the CCN team (Songy et al, Clin Nucl Med. 2011 Sep;36(9): 776-80), 153 patients received their cardiac scans on an older generation camera and then on the new CZT camera. The data were analyzed retrospectively, comparing image quality and also the final diagnosis.

## **3. RESEARCH OBJECTIVES**

---

### **3.1. MAIN OBJECTIVE**

Compare image quality obtained with the new LEHRS GE collimator with that obtained with a standard Siemens LEHR collimator on bone scan examinations.

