#### **4.4. BENEFIT / RISK**

Participation to this study does not create any additional risk for the patient, since the completion of the 2nd scintigraphy does not change the posology, mode and frequency (single injection) of the injected radiopharmaceutical drug.

The patient will maybe benefit from image quality improvement and an exam review by 2 expert physicians. The only constraint for the patient will be an extended examination time of 15 to 30 minutes, compared to a "standard" examination, without any further invasive procedures or additional irradiation.

Collectively, image quality improvement with this collimator could reduce the duration of exams and/or the posology of radiopharmaceutical drugs (improvement of patient dosimetry).

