### 5.5.1. Drawing of lots

A draw will not be carried out because the standard examination will always be carried out first in order not to cause a loss of chance if the examination is stopped (patient with pain...). This also allows the patient to refuse to participate in the study at the end of his or her standard examination. The protocol will be adapted to compensate for the delay between the two examinations (increased acquisition time in proportion to the radioactive decrease).

Patients will be included consecutively. Images will be realized first on the GE camera, equipped with the LEHRS collimator, or on the Siemens camera, with LEHR collimator, depending on his initial appointment slot. However, when 50% of the study population has been achieved on one of the two cameras, the inclusions will only continue on the other.

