### 5.5.2. Blinding method

[figure not shown]

The imaging data will be anonymized, by a person who will not be part of the image reviewers, to remove all information related to the patient's identity from the DICOM fields of the image (metadata). A number will be assigned to each patient, using a randomization table. The patient's identity - anonymization number correspondence will be collected in a specific database.

Images will be read at the end of the inclusions, from the anonymized data, by two senior doctors, on a post-processing console. The anonymization method will not identify the patient's identity or the type of device used (LEHR or LEHRS collimator).

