### **7.1. PROCEDURES IN PLACE FOR RECORDING AND REPORTING ADVERSE EVENTS**

As this is a category 2 study, no particular vigilance related to the research protocol will be required.

However, the monitoring and reporting of incidents and incident risks resulting from participation in the study will be reported through usual channels. As the collimator and the software used are CE marked, any adverse events will be the subject of a material report by ORLEANS CHR.

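### Each collimator is imaged on only one vendor's camera, so the trial compares two imaging systems and cannot support a conclusion about the collimator alone

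*Protocol*

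**What the plan says.** The title, the main objective and the main criterion all make the collimator the compared factor. Section 3.1 reads: "Compare image quality obtained with the new LEHRS GE collimator with that obtained with a standard Siemens LEHR collimator on bone scan examinations". Section 3.3 scores each image type per collimator and compares the percentage of good-quality examinations on the same basis.

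The hoped-for benefit is credited to the same component. Section 4.4 says that "image quality improvement with this collimator could reduce the duration of exams and/or the posology of radiopharmaceutical drugs", and the Executive Summary makes a similar statement.

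On how the images are obtained, the Executive Summary says: "The patient's scans will be performed on 2 separate devices and the images obtained will be compared". Section 5.5.1 is more specific: "Images will be realized first on the GE camera, equipped with the LEHRS collimator, or on the Siemens camera, with LEHR collimator", with the order depending on the appointment slot.

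On software, section 2 says of LEHRS: "The expected degradation of the resolution is compensated by computer correction algorithms". Section 7.1 mentions software beside the collimator ("As the collimator and the software used are CE marked").

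Section 5.1 describes a non-inferiority study with comparisons within each patient.

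**The concern.** The stated question is about a collimator, but the contrast observed is between two devices from different manufacturers. If the GE camera contributes to image quality in its own right, that contribution is counted as a collimator effect. In a non-inferiority study this can work in either direction: a better camera could mask a poorer collimator, or a poorer camera could hide a good one.

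What is at stake is the meaning of the conclusion. Section 2.3 says that no study has yet evaluated this collimator, so this trial would be the first evidence on it. A result reported as a property of LEHRS would be read as applying to LEHRS on other cameras, and the benefit statements on shorter examinations or lower injected activity invite that reading. The patient images cannot show it.

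**Working it through.** There is no figure to reproduce. The point concerns what the contrast identifies, so the check is structural.

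**Step 1. Inputs.** Objective and criterion: sections 3.1 and 3.3. Camera carrying each collimator: section 5.5.1. Two separate devices: Executive Summary. Correction algorithms: section 2.

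**Step 2. Which combinations are imaged.**

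| | LEHRS | LEHR |
|---|---|---|
| GE camera | imaged | not described |
| Siemens camera | not described | imaged |

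Two of the four combinations are imaged, on one diagonal. Whenever the collimator changes, the camera changes with it.

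**Step 3. What a paired difference contains.** For any image type, write the expected within-patient difference (LEHRS image minus LEHR image) as

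D = collimator effect + camera effect + correction effect (where a correction is applied).

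Two imaged combinations give two means. One fixes the overall level, which leaves 2 − 1 = 1 contrast. Even without the correction, two unknowns (collimator and camera) share that single contrast. Only their sum can be estimated.

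**Step 4. Does sample size help?** The Executive Summary plans 85 patients, 70 of them for bone scans. Each of the 70 bone-scan pairs carries the same sum. More pairs would estimate the sum more precisely but would not divide it.

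**Step 5. Does another design feature help?**

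- Pairing within patient (5.1) removes differences between patients. Camera and collimator still change together inside the pair.
- The 50% rule in 5.5.1 ("when 50% of the study population has been achieved on one of the two cameras, the inclusions will only continue on the other") balances which camera is used first. It does not cross cameras with collimators.
- Blinded reading (5.5.2) addresses reader expectation. Its wording treats device and collimator as the same thing: "The anonymization method will not identify the patient's identity or the type of device used (LEHR or LEHRS collimator".
- The DaTQUANT analysis (3.4) gives a common analysis tool, but only for the secondary DaTSCAN ratios.
- The phantom evaluation (2.3, 3.2, 3.4) is secondary. The text does not say whether it uses a common camera or uncorrected data.

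**Step 6. The correction algorithms.** Section 2 makes them part of how LEHRS is meant to perform. It does not say whether whole-body, static or tomographic images receive the correction. The correction term in Step 3 may therefore be absent for some image types. The camera term is present for all of them.

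**The case against.** The strongest reply is that the protocol discloses the bundled comparison. Both vendors are named in the title, objective and main criterion; the Executive Summary says that two devices are used; section 5.5.1 names the camera under each collimator; and section 2.3 likens the work to a study of an older camera against a newer one, which is a whole-device comparison. The objective can then be read as shorthand for two configurations, and the benefit statements are hedged.

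Part of this stands. Nothing is concealed, and a comparison of systems is a legitimate question. But no section says that the conclusion will be at system level, while sections 3.3, 4.4 and 5.5.2 treat the collimator as the factor. Disclosing the set-up does not tell the reader which conclusion is allowed. A separate statistical analysis plan could not repair this, because analysis cannot separate aliased factors.

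A reader might also infer stronger claims, which the document does not support:

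- *That detector, acquisition settings and processing differ in every pair.* Only collimator and camera are documented to differ in all pairs. Section 5.6 records acquisition parameters but does not say they differ by vendor. The adjustment of acquisition time in 5.5.1 is for radioactive decay between the two examinations.
- *That a favourable result could be due entirely to the algorithm.* The image types corrected are not stated, so this cannot be asserted for the whole-body or static images.
- *That the phantom work certainly fails to isolate the collimator.* Its methods are given only in outline, so its design on this point is unknown.

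**Conclusion.** The point holds for collimator and camera. They are fully aliased in every patient pair, so non-inferiority of the collimator as such cannot be identified from the patient images at any sample size. The correction algorithms are a possible further component, of unknown extent by image type. The size of the camera contribution cannot be estimated from the document, and nothing here shows that it is large or in which direction it acts.

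The comparison is not invalid. It remains a proper paired comparison of GE camera with LEHRS against Siemens camera with LEHR, and the fault lies in attributing the result to one component. The change is worth making because it alters what the trial may conclude at almost no cost.

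This rests on the wording of section 5.5.1 and the Executive Summary. The figures in section 5.5 are not shown, but that wording is explicit about which camera carries which collimator.

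**What to change.** 1. Restate the main objective, main criterion and permitted conclusion as: *GE camera with LEHRS and any correction algorithm applied versus Siemens camera with LEHR*.
2. Remove collimator-only attribution from the expected benefits in the Executive Summary and section 4.4.
3. Optionally, in the planned phantom measurements, report LEHRS spatial resolution with and without the correction algorithm, where the software allows it to be switched off. Resolution is the relevant measure, because section 2 ties the algorithm to resolution. This would show the software's part on phantoms. It would not separate collimator from camera in patients.

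Items 1 and 2 are wording only: no test, endpoint, sample size or patient procedure changes. The downside is a narrower claim. Item 3 adds some processing within phantom work that is planned, and assumes the correction can be disabled. If the sponsor wants a conclusion specific to the collimator, wording is not enough; a comparison of collimators on a common camera would be needed.
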